### Outcomes

#### Data collection

All data apart from PROMs (which are automatically sent out to participants via e-mail) is entered directly into REDCap© by a trial worker directly involved in the trial.

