#### Baseline data

The baseline data collected includes patient demographics such as sex, age, work (and work status), arm dominance, height/weight, tobacco and alcohol habits, and list of current diseases, American Society of Anesthesiologists (ASA) grade, mechanism of injury, radiographs, previous surgeries and injuries in the affected shoulder. The following baseline questionnaires will be filled in digitally: Preinjury Disabilities of the Arm, Shoulder and Hand (DASH), University of California, Los Angeles (UCLA) activity scale, European Quality of Life, 5 Dimensions, 5 Levels (EQ-5D-5L) scores. Shoulder pain via an 11-point visual analog scale (VAS).

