### Statistical analysis

The primary outcome is the DASH score at 1 year while under observation, regardless of deviations from assigned treatment or other concomitant treatments. The noninferiority limit will be tested at a 1-sided alpha = 0.025.

The primary analysis will use linear regression for all observed post-randomization measurements, with the participant as a random effect, and the baseline DASH score, randomized treatment, visit number, and the treatment–visit interaction as fixed covariates. The results are presented as the estimated mean difference in the DASH score at 1 year with 95% confidence intervals, the 1-sided *p* value for noninferiority, and the 2-sided *p* value for differences from zero.

The primary model is unbiased for data that are missing at random conditional on the treatment arm, baseline, and a normally distributed individual baseline- and visit-adjusted mean DASH. The impact of missing data will be investigated via sensitivity analyses, which assume a continuum of nonrandom differences between observed and missing data. No imputation will be used.

Supplementary analyses will target the biological efficacy of nonsurgical versus surgical treatment through adjusted per-protocol analyses.

Secondary outcomes will be interpreted as supportive of the primary and analyzed without formal multiplicity adjustment. DASH comparisons for nonprimary timepoints will be taken from the primary analysis. VAS data will be analyzed via the same method as the primary analysis (adjusting for their respective baseline). Likert-scale outcomes will be analyzed via proportional odds logit regression adjusted for baseline as a categorical variable, separately for each timepoint. Complications, radiographic healing, and return to work and activities will be presented descriptively. A detailed statistical analysis plan (SAP) will be finalized before analysis.

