## Participant withdrawal

If a patient withdraws their consent, they can still be included in the statistical analysis if baseline data have been collected, and the impact of missing data will be analyzed in sensitivity analyses as described in the Statistical analysis section above.

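### An unlimited no-imputation rule, with baseline DASH as a covariate, drops randomised patients who have follow-up DASH but no preinjury score

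*Protocol article*

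**What the plan says.** Under Statistical analysis, the article specifies the primary model as follows: "The primary analysis will use linear regression for all observed post-randomization measurements, with the participant as a random effect", with "the baseline DASH score, randomized treatment, visit number, and the treatment–visit interaction as fixed covariates". The next paragraph says that the model is unbiased under a missing-at-random condition given arm, baseline and an individual random effect. It announces "sensitivity analyses, which assume a continuum of nonrandom differences between observed and missing data" and closes with "No imputation will be used". That sentence is not restricted to outcomes. A detailed SAP is to be finalised before analysis.

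The baseline covariate is a recalled preinjury score: "The following baseline questionnaires will be filled in digitally: Preinjury Disabilities of the Arm, Shoulder and Hand (DASH" (Baseline data). Under Data collection, the patient-reported measures are described as going to participants automatically by e-mail. Under Recruitment, randomisation follows documented consent, and a completed baseline form is not named as a condition. Under Data management and safety, a researcher checks questionnaires for completeness and helps participants finish them.

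On patients who withdraw consent, Participant withdrawal says that "they can still be included in the statistical analysis if baseline data have been collected", and refers the effect of missing data to the sensitivity analyses.

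**The concern.** A regression cannot use a row whose covariate is missing. If baseline DASH is a covariate and nothing may be imputed, a patient without a preinjury score loses every follow-up row, including the 1-year primary outcome. This conflicts with the undertaking to analyse "linear regression for all observed post-randomization measurements". It also removes randomised patients from an analysis meant to follow assignment regardless of treatment deviations, and does so for want of a variable that is there mainly for precision.

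This is a stated rule and not a gap left to the SAP. An SAP that kept these patients would have to depart from the published sentence or change the stated model. The stakes are some lost precision and the avoidable exclusion of patients whose primary outcome is known.

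A smaller matter is the withdrawal section, which names baseline data as the condition for inclusion. What the primary model needs is baseline plus at least one follow-up DASH.

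**Working it through.** **Inputs from the article (Sample size).** Margin 10.4, SD 14.3, one-sided alpha 0.025, power 90%, 80 evaluable patients, 20% attrition, total 100. Allocation is 1:1 (Randomization).

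**Assumptions, not in the article.** Share m of evaluable patients without preinjury DASH: 2%, 5% or 10%. Correlation r between baseline and 1-year DASH: 0 or 0.3.

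**1. The plan's figure.** n per arm = 2 × 14.3² × (1.960 + 1.282)² / 10.4² = 39.7, so 40 per arm and 80 in all; 80/0.8 = 100. The figure reproduces. The planned standard error of the difference is 14.3 × √(2/40) = 3.20. With the noncentral t distribution, power at 40 per arm is 89.5%.

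**2. What the literal rule does.** The stated model was fitted without imputation to made-up data on 100 patients with four follow-up visits.

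| Patients | Number | In the model? |
|---|---|---|
| No baseline DASH, follow-up observed | 5 | No |
| Baseline only, withdrew before any follow-up | 3 | No (no outcome row) |
| Withdrew after the 6-week visit | 2 | Yes |
| Complete | 90 | Yes |

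The model used 92 patients.

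**3. Cost if baseline explains nothing (r = 0).** The number per arm becomes 40(1 − m), and SE = 14.3 × √(2/n). Recruitment needed to keep 80 in the model is 80 / (0.8 × (1 − m)), rounded up.

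| m | In model | Power | Recruits for 80 in model |
|---|---|---|---|
| 0 | 80 | 89.5% | 100 |
| 2% | 78.4 | 88.9% | 103 |
| 5% | 76 | 87.9% | 106 |
| 10% | 72 | 86.1% | 112 |

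**4. Cost if baseline explains something (r = 0.3, m = 10%).** Adjustment multiplies the residual variance by 1 − 0.3² = 0.91.

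- Complete baselines: 14.3 × √0.91 × √(2/40) = 3.05.
- Deletion: 14.3 × √0.91 × √(2/36) = 3.22.
- Pooled-mean filling: the 90% with a score have variance factor 0.91 and the 10% without have 1, so the average is 0.919, and 14.3 × √0.919 × √(2/40) = 3.07.

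A simulation of 4,000 covariance-adjusted trials of 80 patients gave 3.03, 3.20 and 3.05 respectively, and filling added no bias. Deletion therefore gives back roughly what adjustment gained and returns the trial to its planned standard error of 3.20. Filling keeps nearly all of the gain.

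Steps 3 and 4 treat the 1-year comparison as a single adjusted contrast. The repeated-measures model will differ somewhat, but it drops the same patients.

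**The case against.** The strongest reply is that a missing covariate is normally SAP detail and that an SAP is announced. In its paragraph, the no-imputation sentence follows a discussion of missing DASH outcomes and a missingness condition that takes baseline as observed, so it may never have been meant for covariates. That is a fair account of the likely intention and a reason to expect an easy correction. It does not change what the sentence says: the rule has no limit, and the SAP would have to contradict it.

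The reply on size stands in large part. No missing-baseline rate is documented, the form belongs to an in-person inclusion process, and completeness is checked. However, the article does not say that the check must be finished before randomisation, so the rate need not be zero.

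A reader might infer a real threat to power from the fall to 86.1%. The article does not support that. The figure deletes patients for lacking a covariate and then gives no credit for the covariate. The article itself calls the unadjusted t-test a pessimistic approximation, and at r = 0.3 the planned precision survives deletion. Nor is there evidence that deletion would bias the comparison.

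A reader might also infer that the withdrawal section promises to analyse patients whom the model cannot use. It does not. It says that they can be included, not that they will be in the primary model, and it points to the sensitivity analyses. Patients who withdraw after giving a follow-up DASH do contribute. Sensitivity analyses over a range of departures can count baseline-only patients without formal imputation.

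**Conclusion.** The point holds as a badly fixed rule with a probably small effect. Read literally, the primary analysis excludes randomised patients with observed follow-up DASH whenever the preinjury DASH is missing, against the section's own undertaking to use all observed follow-up scores. At an assumed 2% to 10% missing, the worst case (baseline uninformative) costs about 0.6 to 3.4 percentage points of power from 89.5%. At r = 0.3 and 10% missing, the cost is a standard error of about 3.2 in place of about 3.05, with no shortfall against the planned 3.20. Both the rate and the correlation are assumptions. The case for change rests less on power than on keeping known primary outcomes in the analysis when a better rule costs almost nothing. The withdrawal wording is a minor clarification and not a contradiction in the plan.

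**What to change.** Before the SAP is finalised:

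1. Limit the no-imputation sentence to post-randomisation outcomes.
2. Add that a missing preinjury DASH is replaced by the mean of all observed preinjury scores, both arms pooled, so that every randomised patient with at least one follow-up DASH is analysed. An equivalent arm-blind method, such as a missing-value indicator or placing baseline in the response vector, would also serve.
3. Reword Participant withdrawal: withdrawn patients contribute the follow-up DASH recorded before withdrawal, and those with baseline data only enter through the sensitivity analyses.

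This takes a few sentences. It needs no new data, leaves the sample size of 80 evaluable and 100 total as it is, and does not affect blinding. Requiring the baseline form before randomisation would reduce the problem for future patients, but recruitment began on 1 September 2025, so a rule for those already enrolled is still needed.

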### Blinding

As this is a surgical vs nonsurgical treatment trial, it is not feasible to blind patients or surgeons to the treatment allocation. The statistical analysis will be performed by a blinded biostatistician not connected to the project apart from the statistical analysis.

### Interim analysis

A blinded sample size re-estimation [63] will be performed in the case of slow recruitment to determine if the target sample size can be adjusted. The inclusion rate will be monitored by the Data and Safety Monitoring Committee (DSMC) (composition is outlined below) as well as the TSC.

There will not be an interim analysis on the primary outcome (DASH), and the reasoning is that no study has as of yet indicated a clinically significant difference in outcome between surgical and nonsurgical treatment. However, the DSMC will monitor the complication frequency in both treatment arms at predefined intervals and may advise the TSC on premature termination of the study if there is a gross imbalance in complication frequency. The DSMC will schedule a meeting shortly after study enrollment begins to agree on monitoring frequency. The DSMC will operate independently from the rest of the study group.

## Protocol violation

Divergence from the protocol reduces the quality or completeness of the data, impacts the safety or health of the participants, or invalidates the informed consent form. Examples include the following: lack of informed consent; inappropriate inclusion or exclusion; unreported AEs or SAEs; inadequate record keeping, including the handling of identification data; noncompliance from the participants; and intentional deviations from the protocol, regulations, or good clinical practice on the part of the study personnel.

Protocol violation also occurs if any of the following occurs:Loss to follow-up.Treatment crossover outside the predefined period.

Patients who meet these criteria will remain in the study but will be omitted from the per-protocol analysis.

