#### Crossover

In line with recent evidence regarding midshaft clavicle fractures and the development of symptomatic nonunion [34, 35], we intend to include the option of crossover to surgical treatment at the 6-week follow-up visit in the nonsurgical study arm if there are signs of the patient being at risk for symptomatic nonunion (severe persisting pain, no healing on radiographs) and if the patient requests surgery. Time from decision to surgery should be within 3 weeks.

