### Sample size

To make an accurate sample size prediction, estimates in standard deviation (SD) scores for the DASH were acquired for the study population. As we found no study that explicitly studied these values for the DASH in patients with LCFs, a number of sources were used, including several RCTs [27, 50–52], as well as studies on different populations of the USA [53], Norway [54], and Germany [55]. Using the numbers from the studies above, we estimated that the mean SD for DASH is 14.3 for those aged 18–65 years. The minimal clinically important difference (MCID) was estimated using an extensive literature review and estimated as 10.4 [37–39, 56–61].

A sample size calculation was performed by a biostatistician at Uppsala Clinical Research Center (UCR) for the study, assuming a 20% attrition rate (an estimate on the basis of data from the SWIFFT trial (where a similar multicenter, pragmatic design was used) [62], the FISH trial [50], and the SHAFT trial [51]).

Since we have limited data on the correlations between the baseline and on-treatment DASH values, we calculate power for an unadjusted t-test, which approximates the primary baseline-adjusted mixed-effect model under a pessimistic scenario and provides a conservative estimate. Assuming a noninferiority limit of 10.4 (MCID), a one-sided alpha of 0.025, 90% power, and SD values of 14.3, a study population of 80 is needed. With an expected attrition of 20%, the total population becomes 100. The calculations were performed via R v. 4.2.3 and the base stats package.

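### The per-protocol set describes nonsurgical care with early rescue, minus some of its failures, not the biological efficacy it is said to target

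*Protocol article*

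**What the plan says.** Three sections of the protocol article bear on this.

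- **Crossover** gives patients the "option of crossover to surgical treatment at the 6-week follow-up visit in the nonsurgical study arm". It is offered when pain remains severe, the radiograph shows no healing and the patient asks for surgery. The operation should follow within 3 weeks of the decision, so the window runs from about week 6 to week 9.
- **Protocol violation** lists loss to follow-up and "Treatment crossover outside the predefined period" as violations. The consequence is: "Patients who meet these criteria will remain in the study but will be omitted from the per-protocol analysis".
- **Statistical analysis** states the purpose: "Supplementary analyses will target the biological efficacy of nonsurgical versus surgical treatment through adjusted per-protocol analyses". The primary analysis in the same section counts every patient as randomized, whatever treatment was actually received.

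**The concern.** The omission rule and the stated target do not fit together. Surgery inside the window is not a violation, so an operated patient's 1-year DASH counts as a nonsurgical result. Surgery after the window is a violation, so patients who struggled on without surgery and were operated on late are removed. The first feature mixes surgical results into the nonsurgical group. The second selects on a post-randomization course that is probably related to outcome. Adjustment for baseline covariates undoes neither.

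Loss to follow-up is a separate and smaller matter. Omitting these patients discards DASH values already observed, which the planned mixed model could use under missing at random.

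At stake is the usual role of such an analysis in a noninferiority trial. Readers look to it to see whether crossover has masked a real deficit. A set that keeps the in-window crossovers and drops late failures is poorly suited to that check.

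**Working it through.** **1. The plan's own figure.** Inputs from Sample size: "a one-sided alpha of 0.025, 90% power, and SD values of 14.3", and a margin of 10.4 DASH points. Per arm, n = 2 × (1.960 + 1.282)² × 14.3² / 10.4² = 39.7, rounded up to 40. This gives 80, as stated: "a study population of 80 is needed". With 20% attrition, 80 / 0.8 = 100, also as stated: "With an expected attrition of 20%, the total population becomes 100". An exact t calculation gives 41 per arm, with 89.5% power at 40. The sample size is not in question; it fixes the scale for what follows.

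**2. Who is in the nonsurgical per-protocol group.**

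| Nonsurgical-arm patient | Per-protocol set |
|---|---|
| Never operated | kept |
| Operated in the window | kept, as nonsurgical |
| Operated after the window | omitted |
| Operated before 6 weeks | omitted |
| Lost to follow-up | omitted |

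This follows from the text and needs no assumption about outcomes.

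**3. Direction.** Take a higher DASH as worse and differences as nonsurgical minus surgical. Let e and l be the shares of the nonsurgical arm with early (in-window) and late crossover. Let D be their excess DASH at 1 year if never operated, rE and rL the fractions of that excess left after early and late surgery, and b the difference for all other patients.

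- No-surgery contrast: b + (e + l)D
- Treatment policy: b + e·rE·D + l·rL·D
- Per-protocol as written: b + e·rE·D / (1 − l)

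The first minus the third is (e + l)D − e·rE·D / (1 − l). If rE ≤ 1, this is at least lD(1 − e − l) / (1 − l), which is positive whenever D is. So the per-protocol estimate falls below the no-surgery contrast if crossovers would have done worse unoperated and early surgery does not harm.

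**4. Size, by assumption only.** The documents give no crossover rates and no outcomes after crossover. With D = 20, e from 5% to 20%, l of 5% or 10%, and several values of rE and rL, the shortfall ranges from about 0.8 (e = 0.20, l = 0.05, rE = 1: 5.00 − 4.21) to 6.0 points (e = 0.20, l = 0.10, rE = 0: 6.00 − 0).

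Main scenario: e = 0.10, l = 0.05, rE = 0.25, rL = 0.75, with the no-surgery difference set to 10.4.

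- b = 10.4 − 0.15 × 20 = 7.4
- Treatment policy: 7.4 + 0.50 + 0.75 = 8.65
- Per-protocol: 7.4 + 0.50 / 0.95 = 7.93

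Simulated t-tests (8,000 runs, 40 per arm before omissions, SD 14.3, no covariate adjustment, no loss to follow-up), with the true no-surgery difference at the margin throughout:

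| e, l, rE, rL | Treatment-policy difference | Per-protocol difference | False noninferiority: treatment policy | As written | All crossovers dropped |
|---|---|---|---|---|---|
| .05, .05, .25, .75 | 9.40 | 8.66 | 4.8% | 7.5% | 8.8% |
| .10, .05, .25, .75 | 8.65 | 7.93 | 7.6% | 11.1% | 14.2% |
| .10, .10, .25, .75 | 8.40 | 6.96 | 9.1% | 17.8% | 21.5% |
| .10, .05, .50, 1 | 9.40 | 8.45 | 5.3% | 9.0% | 14.9% |
| .10, .05, 1, 1 | 10.40 | 9.51 | 2.9% | 5.0% | 14.2% |

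Had no one been operated on, the simulated rate was 2.5% to 2.9%. In the last row early surgery brings no benefit; removing late failures alone still moves 10.4 to 9.5. The last column shows that simply dropping every crossover is worse.

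**5. Would a complier-average estimate recover the contrast?** Assume 1-year means of 10 (surgical), 12 (healed without surgery), 35 (failed, unoperated) and 15 (failed, operated), with 15% early and 10% late crossover.

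- No surgery: 0.75 × 12 + 0.25 × 35 − 10 = 7.75
- Treatment policy: 0.75 × 12 + 0.25 × 15 − 10 = 2.75
- Per-protocol as written: (0.75 × 12 + 0.15 × 15) / 0.90 − 10 = 2.50
- Complier-average, if all surgical-arm patients are operated on: 2.75 / (1 − 0.25) = 3.67

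It does not: 3.67 is less than half of 7.75.

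**The case against.** The strongest reply is that the set matches the intervention as designed. The Abstract describes allocation with optional early crossover, and Objectives counts early detection and treatment of symptomatic delayed union as part of what is compared. A patient operated on in the window has followed the protocol. This stands: keeping such patients is right for a strategy comparison, and a reader who infers that their retention is itself the error goes too far. The fault lies in the label, and in omitting late failures even from the strategy.

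The analysis is also supplementary, and no decision rule depends on it. That stands and limits the consequence.

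The omission rule names no arm. It also removes nonsurgical patients operated on before 6 weeks, perhaps from preference, and arguably surgical-arm patients never operated on. The documents therefore do not support saying that only late failures in one arm are removed. Selection driven by failed healing is nevertheless mainly a matter for the nonsurgical arm.

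The planned analyses are adjusted, by a method that may be set out in the SAP. Suitable weighting could reduce the bias from omitting late crossovers. It cannot make an operated patient's score a nonsurgical one while that patient is kept as nonsurgical.

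Finally, excluding patients lost to follow-up from a per-protocol set is conventional, and the primary model already uses their observed data. That part is minor.

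**Conclusion.** The mismatch is established from the text: the set defined under Protocol violation cannot estimate the target named under Statistical analysis. The lean towards noninferiority is an inference. It holds relative to the no-surgery contrast, provided that late-operated patients would do worse than average unoperated and that early surgery does no harm. All magnitudes above rest on assumed inputs.

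A reader might infer that this analysis will confirm noninferiority whatever the truth. That is not shown: in the scenarios, false noninferiority is raised to about 5% to 18%, which is far from certain. Nor is the per-protocol estimate always below the treatment-policy one. If late surgery fully restores function by 1 year, the two are about equal; in the illustration with assumed means they differ by only 0.25 points (2.75 − 2.50). A reader might also infer that the trial's main conclusion is compromised, but the primary treatment-policy analysis does not use this set. The point is a should-fix.

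**What to change.** 1. **Rename and repair the present analysis.** Call it adherence to the allocated strategy, meaning nonsurgical care with optional early crossover versus surgery. Keep patients operated on late for failed healing as an outcome of the nonsurgical strategy; the reason for surgery must be recorded to identify them. Remove loss to follow-up as an exclusion, so that observed DASH values enter the mixed model under missing at random.
2. **If biological efficacy is still wanted, give it its own estimator.** Treat any surgery in the nonsurgical arm as an intercurrent event. One option is to censor at crossover with inverse-probability weights that use 6-week pain and radiographic status. Present it as supportive, with its assumptions stated.
3. **Two shortcuts to avoid.** Do not simply drop all crossovers. Do not present a complier-average estimate as the no-surgery contrast, since it treats rescue surgery as equal to primary surgery.

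The cost is rewording of Statistical analysis and Protocol violation, matching SAP text and some extra analysis; no more patients are needed. The SAP is due before analysis and recruitment is expected to run to the end of 2028, so the change can be made before outcomes are known. The downside is a wider and possibly unstable interval for the efficacy estimate. The weighting variables are the crossover criteria themselves, and with about 40 evaluable patients per arm, 10% early crossover is only 0.10 × 40 = 4 patients.

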**Methods:**

This is a pragmatic, noninferiority, preference-tolerant, randomized controlled trial (RCT). A total of 100 patients between the ages of 18 and 65 with displaced lateral clavicle fractures will be randomly allocated on a 1:1 ratio to surgical or nonsurgical treatment with the option of early crossover after 6 weeks. An observational cohort will comprise patients not willing to be randomized. This is a multicenter Scandinavian RCT including hospitals in Sweden, Norway, Denmark, and Finland. The primary outcome is the Disabilities of the Arm, Shoulder and Hand (DASH) score at 1 year. Follow-up points will be 6 weeks, 3 months, 6 months, and 1 year. The secondary outcomes are the DASH score, the EQ-5D-5L score, the University of California, Los Angeles (UCLA) activity score, the Nottingham Clavicle Score (NCS), a visual analog scale (VAS) for pain, and anchor questions in the form of the Patient Global Impression of Change (PGIC) collected at all timepoints during the study. All complications, radiographic healing, and return to work will be reported.

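### Loss to follow-up is a ground for exclusion from the supplementary per-protocol analysis, so DASH data from patients treated as allocated are discarded

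*Protocol article*

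**What the plan says.** The Protocol violation section first gives a general definition with examples. Some concern trial administration: "unreported AEs or SAEs; inadequate record keeping, including the handling of identification data; noncompliance from the participants". It then adds two specific grounds: "Protocol violation also occurs if any of the following occurs:Loss to follow-up.Treatment crossover outside the predefined period". It closes with the consequence: "Patients who meet these criteria will remain in the study but will be omitted from the per-protocol analysis".

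The Statistical analysis section gives the purpose of the affected analysis: "Supplementary analyses will target the biological efficacy of nonsurgical versus surgical treatment through adjusted per-protocol analyses". For the primary analysis it states: "The primary analysis will use linear regression for all observed post-randomization measurements, with the participant as a random effect". It justifies that model by its behaviour with incomplete data: "The primary model is unbiased for data that are missing at random conditional on the treatment arm, baseline", together with a normally distributed individual mean DASH. Sensitivity analyses for nonrandom missingness are planned as well. The Participant withdrawal section lets patients who withdraw consent stay in the statistical analysis if baseline data were collected.

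**The concern.** A per-protocol analysis aimed at biological efficacy should select patients on eligibility and on the treatment they received. A patient who was treated as allocated, answered the DASH at 6 weeks, 3 months and 6 months, and then could not be reached has departed from nothing that bears on efficacy. The written rule removes that patient and all the scores.

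Two things follow. The per-protocol analysis loses information that the primary model was chosen to use. It also selects on an event that may depend on how the patient was doing. If patients with poor interim scores leave one arm more often, those who remain look too good in that arm. Where that arm is the nonsurgical one, the error runs towards noninferiority.

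The analysis matters because the primary analysis counts outcomes regardless of deviations from assigned treatment, and nonsurgical patients may cross over to surgery at 6 weeks. Readers of a noninferiority trial are likely to look at the per-protocol result for support.

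**Working it through.** **The plan's own figure.** Inputs from the Sample size section: margin 10.4, SD 14.3, one-sided alpha 0.025, power 90%, attrition 20%. With a true difference of 0, n per arm = 2 × (1.960 + 1.282)² × 14.3² / 10.4² = 39.7, rounded up to 40, so 80 in total. Then 80 / (1 − 0.20) = 100. Both figures reproduce. Power at 40 per arm is 90.2% by the normal approximation and 89.5% by the noncentral t.

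**Data discarded.** Attrition of 20% among 100 patients is 20 patients. The abstract gives the visits: "Follow-up points will be 6 weeks, 3 months, 6 months, and 1 year". Three of these precede 1 year, so at most 20 × 3 = 60 DASH values are deleted. This is a ceiling: it is reached only if every lost patient completes all three visits first, and the protocol gives no dropout timing.

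**Bias from deletion, compared with keeping the data.** The protocol does not give the dropout mechanism, so these inputs are assumptions:
- SD 14.3 at each visit, equal correlation ρ between visits (0.3 to 0.7), normal scores, higher DASH worse;
- no true difference between arms;
- nonsurgical arm: 20% lost after 6 months, with the odds of loss doubling per SD of 6-month DASH;
- surgical arm: 20% lost, unrelated to DASH.

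Let z be the standardized 6-month DASH in the nonsurgical arm. The loss probability is 1 / (1 + exp(−(a + 0.693 z))). A value a = −1.52 gives 20% loss overall. Numerical integration then gives a mean z of −0.129 among those retained.

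Under deletion, the shift in the 1-year difference is ρ × 14.3 × (−0.129):

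| ρ | Shift (points) | Share of the 10.4 margin |
|---|---|---|
| 0.3 | −0.55 | 5.3% |
| 0.5 | −0.92 | 8.9% |
| 0.7 | −1.29 | 12.4% |

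The minus sign favours the nonsurgical arm, that is, noninferiority.

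With the earlier values kept, I fitted a random-intercept model with visit, arm and their interaction to simulated data of 20,000 patients per arm. The estimated 1-year differences were 0.05, 0.01 and −0.05 for ρ = 0.3, 0.5 and 0.7. The simulation error is of the order of 14.3 × √(2/16,000) = 0.16, so these are indistinguishable from 0. That result relies on the equal-correlation structure matching the fitted model, and on loss depending only on observed scores.

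**If administrative failings also exclude.** The rate of such violations is not given. The 80 patients left after attrition would shrink further. Power is from the noncentral t, with true difference 0 and SD 14.3:

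| Assumed further exclusion | Patients left | Power |
|---|---|---|
| 0% | 80 | 89.5% |
| 5% | 76 | 87.9% |
| 10% | 72 | 86.1% |
| 20% | 64 | 81.7% |
| 30% | 56 | 76.2% |

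**The case against.** The strongest reply is that the per-protocol analysis is only supplementary. The primary analysis uses all observed DASH regardless of deviations, and the sample size does not change. Robustness to dropout is assigned to the planned sensitivity analyses, not to this one. All of that stands. A reader might infer that the trial's main noninferiority conclusion is biased, or that the protocol names the per-protocol analysis as its test of robustness. The documents support neither.

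A reader might also infer that the rule makes the analysis valid only if data are missing completely at random. That is too strong. The per-protocol analyses are described as adjusted, and an analysis adjusted for arm and baseline tolerates loss that depends only on those. The weakness is loss that depends on DASH during follow-up. Baseline adjustment would not in general remove that, and it cannot restore deleted scores.

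The reading of the closing sentence is open. The administrative items are offered as examples, several describe staff or site conduct, and the sentence follows directly on the two-item list. It may cover only that list. Against this, the linking word in "Protocol violation also occurs if any of the following occurs:Loss to follow-up.Treatment crossover outside the predefined period" puts both lists under one definition. So it cannot be said as fact that a record-keeping failure excludes a patient. Loss to follow-up is in the two-item list and is covered on either reading.

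Loss to follow-up is not defined in the article, and the full protocol may define it. A single missed 1-year questionnaire may not qualify. This limits the count of patients affected, not the mismatch between the rule and its purpose.

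Finally, selecting on treatment received is also selection after randomization. That is true, but it is inherent in a per-protocol question, whereas selecting on loss to follow-up is not.

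**Conclusion.** The point holds for loss to follow-up. The rule is explicit, does not serve the stated aim, and discards data that the protocol's own model can use. The plausible harm is moderate: about 0.6 to 1.3 DASH points towards noninferiority, or roughly 5% to 12% of the margin, against about 0 if the data are kept. That range depends on outcome-related loss in the nonsurgical arm only. With loss unrelated to follow-up DASH the bias vanishes, and with the pattern in the surgical arm instead it reverses. Loss that depends on unobserved scores would leave some bias under either rule.

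For the administrative examples, the finding is an ambiguity. If they are covered, patients treated as allocated would be excluded for reasons unrelated to treatment. The primary analysis and the sample size of 100 stand as they are.

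**What to change.** In the Protocol violation section, and in the SAP before it is finalized:

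1. Remove loss to follow-up as a ground for per-protocol exclusion. Keep those patients' observed DASH values in the same repeated-measures model as the primary analysis.
2. Base exclusion on ineligibility judged from pre-randomization data and on departure from allocated treatment as the protocol already defines it.
3. State that administrative violations (AE reporting, record keeping, handling of identification data) are logged and reported but do not define the analysis set.

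The cost is a few sentences. Sample size, visits and data collection do not change. Recruitment is expected to run to 31 December 2028, so the change can be made well before analysis.
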